**Methods/design:**

Iohexol measured GFR will be the reference against which each estimating equation will be compared. The estimating equations will be based upon serum creatinine and/or cystatin C. The eGFR-C study has 5 components:

1) A prospective longitudinal cohort study of 1300 adults with stage 3 chronic kidney disease followed for 3 years with reference (measured) GFR and test (estimated GFR [eGFR] and urinary albumin-to-creatinine ratio) measurements at baseline and 3 years. Test measurements will also be undertaken every 6 months. The study population will include a representative sample of South-Asians and African-Caribbeans. People with diabetes and proteinuria (ACR ≥30 mg/mmol) will comprise 20-30% of the study cohort.

2) A sub-study of patterns of disease progression of 375 people (125 each of Caucasian, Asian and African-Caribbean origin; in each case containing subjects at high and low risk of renal progression). Additional reference GFR measurements will be undertaken after 1 and 2 years to enable a model of disease progression and error to be built.

3) A biological variability study to establish reference change values for reference and test measures.

4) A modelling study of the performance of monitoring strategies on detecting progression, utilising estimates of accuracy, patterns of disease progression and estimates of measurement error from studies 1), 2) and 3).

5) A comprehensive cost database for each diagnostic approach will be developed to enable cost-effectiveness modelling of the optimal strategy.

The performance of the estimating equations will be evaluated by assessing bias, precision and accuracy. Data will be modelled as a linear function of time utilising all available (maximum 7) time points compared with the difference between baseline and final reference values. The percentage of participants demonstrating large error with the respective estimating equations will be compared. Predictive value of GFR estimates and albumin-to-creatinine ratio will be compared amongst subjects that do or do not show progressive kidney function decline.

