**Figure 1 F1:**
[figure not shown]
General study schema.

There are five components to the study:

1) A 3-year prospective longitudinal cohort study using 6-monthly estimates of GFR and baseline and final reference GFR values to assess and compare the accuracy and precision of each estimate of GFR and change in GFR. This will include assessments in high risk subgroups and ethnic groups.

2) Investigation and modelling of patterns of progression of GFR in a subset of the cohort, stratified by ethnicity, presence of diabetes and proteinuria, who will receive annual reference GFR, assessing risk factors and over time.

3) A sub-study investigating sources of variability to estimate the components of measurement error in each measure and estimate of GFR.

4) Using information from 1), 2) and 3) modelling of alternative monitoring strategies, using different estimates of eGFR and monitoring frequencies.

5) A model-based cost-effectiveness analysis.

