### Prospective longitudinal cohort study

The primary study will comprise a prospective longitudinal cohort study in which adults (n = 1300) with stage 3 CKD, enriched to include people more likely to have progressive kidney disease (i.e. those with proteinuria and/or diabetes), will be recruited from six UK centres. Participants will be recruited from both primary (two centres) and secondary/tertiary (four centres) care. People aged 18 years and older having stage 3 CKD (eGFR measurements between 30 and 59 mL/min/1.73 m^2^ inclusive sustained over at least 3 months prior to recruitment) will be included. Recruitment will be targeted such that 20% to 30% of recruits will have proteinuria (ACR ≥30 mg/mmol) and a similar proportion will have diabetes. The prevalence of proteinuria and diabetes will be monitored during the course of the study to ensure reasonable representation.

Participants will attend hospital in the morning having been advised to consume a light breakfast (no meat or fish). A clinical (including cardiovascular) and drug history will be recorded using a standardised questionnaire. Information on ethnicity will be gathered using a modified version of the 2011 UK Census Questionnaire. Height will be measured to the nearest 0.1 cm with a rigid stadiometer. Body weight will be measured in light indoor clothing to the nearest 0.1 kg. Waist circumference will be recorded to the nearest 0.1 cm at the mid-point between the lower costal margin and the level of the anterior superior iliac crest. Hip circumference will be measured at the widest point of the hips and the maximal protrusion of the gluteal muscles. Brachial blood pressure will be measured three times in the sitting position as recommended [56]. Blood will be taken for serum creatinine, cystatin C and a urine sample will be collected for ACR. Further aliquots of serum, plasma and urine will be stored for potential analysis of future markers of GFR. An iohexol reference GFR measurement will be undertaken in addition to estimation of GFR using four GFR estimating equations (MDRD, CKD-EPI_creatinine_, CKD-EPI_cystatin_, and CKD-EPI_cystatin-creatinine_) (Table 1).

Participants will be followed for three years. All the above measurements and the clinical questionnaire will be repeated at 36 months. At each 6 month interval, all participants will have blood taken for serum creatinine, cystatin C and a urine sample will be collected for ACR. GFR will be estimated as above.

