### Sub-study of patterns of disease progression

At three centres 125 each of Caucasian, African-Caribbean and Asian subjects (i.e. n = 375 in total), stratified in each group by higher and lower risk of disease progression (approximately 60 with diabetes and/or proteinuria and 60 with neither diabetes nor proteinuria) will undergo additional sampling every year over the 3 year study period. At each point indicated subjects will undergo a reference GFR measurement in addition to cystatin C and creatinine eGFRs and ACR. The study will enable a model of disease progression to be developed based on reference GFR measurement enabling optimal monitoring frequencies in a high-risk cohort to be defined. This number of subjects should provide a range of values over the main factors considered to influence disease progression and allow assessment of covariates in the statistical model. Further assessment of covariates will be performed by combining the data from this sub-study with the main study. Inclusions/exclusions and laboratory methods for this sub-study will be as above.

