Models will be constructed to predict time to progression based on baseline eGFRs and ACR. Progression will be defined in terms of decline in reference GFR (change in iohexol GFR > 10 mL/min/1.73 m^2^) or an increase in albuminuria category, as suggested by KDIGO [38]. Progression will only be detected at one of 6 time points, hence piecewise survival models will be fitted to determine whether the prognostic value of ACR and the estimated GFRs is independent of other risk factors. We will develop a prognostic model utilising age, gender, ethnicity, body mass index, waist circumference, mean arterial blood pressure, diabetes mellitus, smoking status, and presence of vascular disease in addition to baseline ACR and the various eGFRs. Both proportional and non-proportional hazards will be considered. Bootstrap validation will be used with these prediction models.

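### Question 3 builds its survival model on six detection times, but iohexol GFR has one post-baseline time in 925 participants and three in 375, so interval-specific hazards and risks before 36 months are distorted

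*Protocol article*

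**What the plan says.** Under Data analysis, Prospective longitudinal cohort study, question 3, the article plans models for time to progression from baseline eGFRs and ACR. An event is an iohexol GFR change of more than 10 mL/min/1.73 m² or a move to a higher albuminuria category. The reason given for the model is: "Progression will only be detected at one of 6 time points, hence piecewise survival models will be fitted". The section adds: "Both proportional and non-proportional hazards will be considered". Bootstrap validation is to follow.

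The measurement schedule is set out elsewhere. The list of study components describes the cohort study as "using 6-monthly estimates of GFR and baseline and final reference GFR values". Under Methods/design, Prospective longitudinal cohort study, the full baseline set, which includes iohexol GFR, comes back once: "All the above measurements and the clinical questionnaire will be repeated at 36 months". The half-yearly visits are lighter: "At each 6 month interval, all participants will have blood taken for serum creatinine, cystatin C and a urine sample", the urine being for ACR. The abstract and the section on the sub-study of patterns of disease progression add iohexol GFR at years 1 and 2 for 375 people, who are a subset of the cohort.

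**The concern.** The count of six drives the choice of model, and it fits only one of the two limbs of the event. In most of the cohort a GFR loss in year 1 cannot be seen before month 36. A model that treats six visits as common detection times would place that event in the last interval.

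Three outputs would then carry the visit schedule as if it were disease: the interval-specific hazards, the comparison of proportional with non-proportional hazards, and any predicted risk before 36 months. A baseline eGFR with a constant effect on GFR loss could appear to have no effect early and a strong effect late. Bootstrap resampling would not expose this, because every resample has the same schedule.

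**Working it through.** **Schedule.** Reproducing the article's figure: 36 months / 6 months = 6 post-baseline visits, or 7 with baseline, which agrees with the maximum of 7 eGFR time points in question 2. Counting by limb:

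| Limb | Participants | Post-baseline detection times |
|---|---|---|
| Albuminuria category | 1300 | 6 |
| Iohexol GFR, outside sub-study | 1300 − 375 = 925 (71.2%) | 1 (month 36) |
| Iohexol GFR, sub-study | 375 (28.8%) | 3 (months 12, 24, 36) |

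Six times for everyone would be 1300 × 6 = 7,800 participant-visits. Iohexol is scheduled at 925 × 1 + 375 × 3 = 2,050 of them (26.3%). Nobody has it at months 6, 18 or 30.

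**Effect on the model.** The documents give no event rates by limb, so these inputs are assumptions: GFR progression with a constant hazard ratio of 2.0 per SD of baseline eGFR; three-year GFR progression of 20-30% at the covariate mean; albuminuria events of 1-4% per visit, unrelated to eGFR; no iohexol measurement error. Sub-study members (375/1300) are given iohexol at months 12, 24 and 36, and everyone else at month 36 only. Each event is dated to the visit where it is first seen, and complementary log-log models are fitted by interval.

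At 20% GFR progression and 2% albuminuria events per visit:

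| Month | 6 | 12 | 18 | 24 | 30 | 36 |
|---|---|---|---|---|---|---|
| Interval hazard, % | 2.0 | 4.5 | 2.0 | 4.1 | 2.0 | 21.1 |
| Interval hazard ratio | 1.0 | 1.5 | 1.0 | 1.4 | 1.0 | 1.9 |

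With GFR seen at every visit, the interval hazard ratios would be flat at about 1.6. They sit below 2.0 because unrelated albuminuria events dilute the effect.

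Two-year composite risk is 12% as dated against 23% true. A hand check:
- Free of albuminuria events after four visits: 0.98⁴ = 0.922.
- Implied population two-year GFR progression: 1 − 0.77/0.922 = 16.5%.
- Only 28.8% of people can show it by then, so the visible part is 0.288 × 0.165 = 4.8%.
- Dated two-year risk: 1 − 0.922 × (1 − 0.048) = 12.2%.

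Over the whole assumed range:
- 44-69% of events fall at month 36.
- Month-36 hazard ratios are 1.8-2.0, against about 1.0 at months 6, 18 and 30.
- Two-year composite risk is about 9-21% as dated, against 20-36% true.

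**What hardly moves.** A single hazard ratio with a free baseline hazard per interval is 1.57, against 1.60 if GFR were seen at every visit. The fall is at most about 0.1 across scenarios. Three-year risk is the same either way in this set-up.

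**A second set of assumptions** points the same way. Take linear GFR decline with mean (SD) of 2 (2) or 3 (3) mL/min/1.73 m² per year, baseline GFR uniform on 30-60, and an iohexol CV of 5.5% (the low end of the range in the Background). Detected GFR progression in the 925 is 0% at two years, while about 7% or 25% have truly crossed the threshold.

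**The case against.** The other side has good points.

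- **Six times is not wholly wrong.** Albuminuria is observed at six visits in all 1300, so the composite can be detected at any of them. This stands: the composite hazard is distorted, not invented by the schedule.
- **No risks at one or two years are promised.** The stated aim is whether ACR and the eGFRs predict independently of other factors, and all four equations face the same schedule. This also stands. A reader might infer that the hazard ratios or the comparison of equations are invalid. The documents do not support that: under proportional hazards the free interval baselines absorb most of the jump.
- **The sub-study softens the effect.** A reader might infer that the first five intervals hold albuminuria events only. That is true of the 925 but not of the modelled cohort, because 375 people can have GFR events dated to months 12 and 24.
- **The likelihood may be set elsewhere.** The article knows that event times are grouped, and a piecewise model can be fitted with interval censoring on personal iohexol dates. That would avoid the misdating, and such detail may sit in an analysis plan that is not shown. But the point here is not missing detail. The article states a premise that its own schedule contradicts and chooses the model from it, and that premise points to six common detection times.
- **Albuminuria events unrelated to eGFR is a convenient assumption.** It fixes the early hazard ratios at 1.0. With a relation they would take the albuminuria association instead. The pattern would still follow the iohexol calendar unless both limbs had the same association.

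**Conclusion.** The point holds in a limited form. The six-time-point statement is correct for albuminuria and wrong for iohexol GFR (one time in 925 people, three in 375, six in nobody). That follows from the article alone.

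If events are dated to the visit where they are first seen, interval-specific hazards, the planned look at non-proportional hazards and any risk predicted before 36 months will reflect the iohexol calendar. The sizes above depend on the assumed event rates and effect; the direction does not.

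The common hazard ratio is only slightly reduced. Three-year risk is essentially unaffected, a result that rests on error-free iohexol values. The sample size calculation and questions 1 and 2 are not touched. The correction should be made, but it does not invalidate question 3.

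**What to change.** - Reword the justification: albuminuria progression can be detected at six visits; GFR progression at month 36, or at months 12, 24 and 36 in the sub-study.
- Analyse the GFR limb in one of two ways: as a yes/no outcome at month 36 from baseline and final iohexol GFR in everyone (logistic or complementary log-log), or with an interval-censored likelihood using each participant's own iohexol dates.
- Keep the 6-monthly discrete-time model for the albuminuria limb.
- State that interval-specific effects, non-proportional effects and risks before 36 months will not be interpreted for visit-dated GFR events.

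No new data are needed. The binary option gives up any time-to-event claim for the GFR limb; interval censoring keeps one, limited to what the iohexol dates can support, for slightly more analysis work.

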#### Sub-study of patterns of disease progression

##### **How does GFR progress over time and what are the optimal monitoring times?**

The rate of decline (mL/min/1.73 m^2^/year) in reference GFR, and the difference between reference GFR and estimated GFRs (referred to as error), measured every 12 months will be modelled over time using a longitudinal linear or nonlinear (exponential decline) random coefficients regression model to estimate average and variability in disease progression and error. Parameters of the model for each outcome will be estimated using maximum likelihood. Covariates to be explored in the model will be as described above. The effect of covariates on the population average intercept and longitudinal time effect parameters will be assessed. The method of backward elimination will be used to remove covariates which are not significant from the model. A linear relationship between disease progression and drug name or drug class will be explored. Analysis will be undertaken using NONMEM version 7.1.2, R open source software and PFIM version 3.2.2 optimal design algorithms (R open source software). The PFIM algorithms will be used to calculate the D-optimal [62] sampling times from the disease progression model based on reference GFR for individuals with diabetes and/or proteinuria, and for those individuals with neither of these conditions. Optimal monitoring strategies will be selected from a set of designs and for important subgroups of the population found to be significant in the disease progression model. The monitoring strategies identified will be used as the basis for further simulations.

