### Sample size calculations

1) Prospective longitudinal cohort study

The sample size calculation for the main study focuses on the ability to detect differences in accuracy of measurement between the MDRD_creatinine_ equation and the CKD-EPI_cystatin C_ equation. We will also make secondary comparisons with the other equations**.** The measure of accuracy we will use is the P_30_. Sample size is based on a simulation study to estimate differences in P_30_ and estimates of rate of change which are not amenable to algebraic solution. Our simulation modelled the full structure of the study including random variability, and computed statistical power through noting the percentage of simulations yielding statistically significant results (P < 0.05) for analysis of each outcome. Power estimates are based on 1000 simulations.

With 1000 evaluable subjects our simulations showed the study to have 87% power at the 5% significance level to detect a difference of 5% in P_30_, between 81% and 86%, which is of a magnitude considered clinically important and likely to occur with the expected scale of differences in imprecision between the equations [27]. We thus aim to recruit 1300 people, which allowing for 15-20% drop-out will deliver over 90% power. The proposed sample size in the ethnicity subgroups will allow P_30_ estimates to be reported with 95% confidence intervals of 10 percentage points wide.

Rates of change in estimated and measured GFR will be obtained by linear regression. Padala et al. proposed two cut-points for estimating accuracy of rates of change: greater than 3 mL/min/1.73 m^2^/year error and greater than 5% error [54]. The study will have over 90% power and over 80% power at the 5% significance level to detect differences in these two outcomes respectively, for differences of a magnitude corresponding with P_30_ measures of 81% and 86%.

2) Sub-study of patterns of disease progression

A sample size of 375 was chosen based on practical considerations to allow investigation of twelve covariates of interest (gender, age, diabetes, duration of diabetes, ethnicity, albuminuria, baseline GFR, blood pressure, body mass index, waist circumference, smoking status and presence of vascular disease) in addition to variables for time, drug effects and random effects. Another consideration was to include a reasonable number of subjects in each of the ethnic groups and high and low risk subgroups to estimate disease progression.

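### Backward elimination in the progression model exempts none of the factors on which the sub-study is sampled, so a moderate ethnic difference in GFR decline would often be set to zero

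*Protocol article*

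**What the plan says.** The Methods/design list of components describes the sub-study as "stratified by ethnicity, presence of diabetes and proteinuria, who will receive annual reference GFR". The Methods section on the sub-study fixes 125 people in each of three ethnic groups, and within each group "approximately 60 with diabetes and/or proteinuria and 60 with neither diabetes nor proteinuria".

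Sample size calculations, item 2, states: "A sample size of 375 was chosen based on practical considerations to allow investigation of twelve covariates of interest". The list includes "gender, age, diabetes, duration of diabetes, ethnicity, albuminuria, baseline GFR, blood pressure", among others. The same item adds that the numbers in the ethnic and risk groups were chosen so that progression could be estimated in them.

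The Data analysis section for the sub-study fits a random coefficients model for measured GFR over time. It says "Covariates to be explored in the model will be as described above", and then: "The method of backward elimination will be used to remove covariates which are not significant from the model". No covariate is named as staying in regardless, and no retention level is given. The same paragraph requires D-optimal sampling times from this model "for individuals with diabetes and/or proteinuria, and for those individuals with neither of these conditions". Strategies for further subgroups are limited to those found significant. Modelling monitoring strategies then takes the patterns and determinants of progression from this sub-study into a simulation of representative cohorts.

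**The concern.** The design pays to have equal ethnic groups and a balance of higher- and lower-risk people so that decline can be estimated in each. The selection rule then lets a significance test replace any of those estimates with zero. The size of 375 rests on practical considerations and not on power, so a non-significant term cannot be read as no difference.

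Two things are at stake:

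- **Ethnicity.** If it is eliminated, no group-specific slope is carried forward. The average slope then describes a one-third mix created by the sampling, and the model holds nothing with which to re-weight it by ethnicity for a representative population. If it survives only because it was significant, its estimate is biased away from zero.
- **Risk group.** Sampling times for the higher- and lower-risk groups are required whether or not the terms are significant. If every term that carries the contrast were eliminated, the two sets of times would lose their direct basis for differing.

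**Working it through.** The sub-study has no power figure to reproduce; only 3 × 125 = 375 can be checked. The rest is illustration, with assumptions marked.

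**Inputs**
- Group size: 125 v 125 for an ethnic contrast (protocol).
- Reference GFR at 0, 1, 2 and 3 years (protocol), so Sxx = 1.5² + 0.5² + 0.5² + 1.5² = 5.
- Within-person CV of 10%: the figure in Sample size calculations, item 3, and inside the 5.5% to 11.6% range in Measuring GFR.
- Mean GFR 45, near the middle of stage 3 (assumed), so the within-person SD is 4.5.
- Between-person slope SD of 2 to 3 mL/min/1.73 m2/year (assumed).
- Two-sided 5% elimination threshold (assumed).

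**Standard error of a slope difference**
SE = √(slope SD² + 4.5²/5) × √(2/125)
- Slope SD 2: √(4 + 4.05) × 0.1265 = 2.84 × 0.1265 = 0.36
- Slope SD 3: √(9 + 4.05) × 0.1265 = 3.61 × 0.1265 = 0.46

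**Chance that a true difference d is retained**, Φ(d/SE − 1.96) plus a negligible opposite tail

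| True difference per year | Slope SD 2 | Slope SD 3 |
|---|---|---|
| 0.8 | d/SE = 2.23, 61% | d/SE = 1.75, 42% |
| 0.5 | d/SE = 1.39, 29% | d/SE = 1.09, 19% |

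**Mean estimate given retention, d = 0.8**, from d + SE × φ(1.96 − d/SE)/Φ(d/SE − 1.96)
- Slope SD 2: 0.8 + 0.36 × 0.385/0.606 = 1.0
- Slope SD 3: 0.8 + 0.46 × 0.390/0.417 = 1.2

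**Wider range.** With between-person SD 1.5 to 4 and CV 5.5% to 11.6%, the total slope SD runs from 1.9 to 4.6. A true ethnic difference of 0.5 is then dropped in 44% to 87% of studies, and one of 1.0 in 1% to 60%.

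**Simulated backward elimination** (12 candidate covariates, n = 375, 300 runs per setting, total slope SD 3.6, assumed overlap between diabetes and proteinuria). With true effects of 1.0, ethnicity was dropped in about 36% of runs, diabetes in 38% and albuminuria in 30%.

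**Risk contrast.** The simulation also counted runs in which diabetes, its duration and albuminuria were all dropped, at the same total slope SD of 3.6:
- about 44% with effects of 0.5;
- about 2% with effects of 1.0;
- none with diabetes and albuminuria effects of 1.7.

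The value 1.7 comes from Progression of kidney disease in the Background: 3.6 − 1.9 = 1.7 in men and 2.8 − 1.1 = 1.7 in women. As a direct check, take 187 v 187, with the two total SDs above. Then z = 1.7/(2.84 × √(2/187)) = 5.8 and 1.7/(3.61 × √(2/187)) = 4.6, so retention exceeds 99%.

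**The case against.** The strongest reply is that these are sampling strata and not randomisation strata. The Methods section says that the spread of subjects is meant to allow covariates to be assessed, and testing them does not contradict that. For ethnicity the text is consistent with itself: further monitoring subgroups are used only if significant. The Methods also promise further covariate assessment by pooling with the main cohort, which the 125 v 125 calculation leaves out. The threshold and the base-model terms could be set in an analysis plan that is not shown.

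Much of this stands as a limit on severity. It does not remove the point. The selection rule is stated, not left open, and it exempts nothing. Item 2 of the sample size section gives estimation within groups as a reason for the numbers. Pooling adds information but protects no stratification factor from elimination.

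A reader might infer two stronger things that the article does not support:

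- **That losing either diabetes or albuminuria alone would make the two risk-group designs identical.** It would not. The higher-risk group is defined by either condition, so the remaining term still separates the groups, and duration of diabetes carries part of the same contrast.
- **That ethnic, diabetic and proteinuric effects on progression are stated objectives and direct inputs to the cost-effectiveness study.** The objectives section concerns the effect of these factors on equation performance, which the main cohort addresses without backward elimination. The health economics section draws on the sub-study only indirectly, by extending the monitoring strategy.

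**Conclusion.** The point holds in a limited form. The rule as written can delete the factors on which the sub-study was sampled, against the article's own reason for the group sizes.

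The practical risk is greatest for ethnicity. Under the assumptions above, a true difference of 0.8 per year has roughly an even chance of being kept, one of 0.5 is usually lost, and retained estimates are inflated. These figures depend on a slope SD and a threshold that the article does not give; the wider range shows how far they can move.

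For diabetes and proteinuria, the direct contrast behind the two sets of sampling times disappears only if diabetes, its duration and albuminuria are all eliminated. That is unlikely if the diabetes effect is near 1.7 per year, and becomes a real possibility only if effects are much smaller.

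**What to change.** State that ethnicity, diabetes and albuminuria (or proteinuria) stay in the progression model as sampling strata, on both the intercept and the time effect, and are reported with 95% confidence intervals whatever their P value. Apply backward elimination only to the remaining covariates, and give the retention level. Carry the stratum estimates into the monitoring simulation so that slopes can be re-weighted to the intended population.

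The cost is a sentence or two of text and no extra participants. With two terms for ethnicity and one each for diabetes and albuminuria, at most 4 × 2 = 8 parameters are held in the model for 375 people. The final model is slightly less parsimonious.
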